### **10.5.3. According-to-protocol (ATP) cohort for analysis of immunogenicity**

The ATP cohort for analysis of immunogenicity will include all evaluable subjects from the Total vaccinated cohort:

- Who meet all eligibility criteria.
- Who comply with the procedures and intervals defined in the protocol.
- Who are within the maximum interval allowed as defined in the protocol. Refer to [Table 11](#) for the interval between study visits that will be considered for inclusion in the ATP cohort for analysis of immunogenicity.
- Who did not receive a product leading to exclusion from an ATP analysis as listed Section [6.7.1](#).
- Who did not present with a medical condition leading to exclusion from an ATP analysis as for Section [6.8](#).
- For whom data concerning immunogenicity endpoint measures are available. This will include subjects for whom assay results are available for antibodies against at least one study vaccine antigen component after vaccination.

## **10.6. Derived and transformed data**

### **Immunogenicity**

- The cut-off value is defined by the laboratory before the analysis and is described in Section [5.7.3](#).
- A seronegative subject is a subject whose titer is below the cut-off value.
  - Anti-CS repeat antibody titers < 0.5 EU/mL.
  - Anti-CS full-length and peptides antibody titers < 200
  - Anti-Ad35 antibody titers < 16 IC90.

- A seropositive subject is a subject whose titer is greater than or equal to the cut-off value for the following antigens:
  - Anti-CS repeat antibody titers  $\geq 0.5$  EU/mL.
  - Anti-CS full-length and peptides antibody titers  $\geq 200$
  - Anti-Ad35 antibody titers  $> 16$  IC90.
- A hepatitis B virus seroprotected subject is defined as a subject whose antibody titer is greater than or equal to the cut-off value for the following antigen:
  - Anti-HBs antibody titers  $\geq 10$  mIU/mL.
- The Geometric Mean Titers (GMTs) calculations are performed by taking the anti-log of the mean of the log titer transformations. Antibody titers below the cut-off of the assay will be given an arbitrary value of half the cut-off for the purpose of GMT calculation.
- Handling of missing data:

For a given subject and a given immunogenicity measurement, missing or non-evaluable measurements will not be replaced. Therefore, an analysis will exclude subjects with missing or non-evaluable measurements.

### Reactogenicity and Safety

- Handling of missing data:
  - Subjects who missed reporting symptoms (solicited/unsolicited or concomitant medications) will be treated as subjects without symptoms (solicited/unsolicited or concomitant medications, respectively). In case of significant non-compliance of study procedures for reporting symptoms, the analysis plan will be reassessed to ensure more accurate reporting of study data by further analysis.
  - For the analysis of solicited symptoms, missing or non-evaluable measurements will not be replaced. Therefore the analysis of the solicited symptoms based on the Total vaccinated cohort will include only subjects/doses with documented safety data (i.e. symptom screen/sheet completed).

## 10.7. Conduct of analyses

Any deviation(s) or change(s) from the original statistical plan outlined in this protocol will be described and justified in the final study report.

### 10.7.1. Sequence of analyses

The analyses will be performed stepwise:

- An interim analysis for futility will be performed on safety and efficacy data collected up to 28 days post-challenge (Study Day 105) for 46 subjects from Cohort A. Refer to Sections 5.4.4.1 and 5.4.4.2 for more details on the futility analysis.
- A primary analysis will be performed on all efficacy, immunogenicity and safety data collected up to 28 days post-challenge (Study Day 105) on all cohorts.

- A final analysis will be conducted at 6 months post-dose 3, including extended safety and immunogenicity follow-up. The final study report will be generated after final analysis.

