#### **5.4.3. Malaria Challenge**

Volunteers from both study groups completing their immunization course will be challenged with sporozoite-infected mosquitoes to determine whether the expected protective response has developed. Such challenges are mandated by the absence of any laboratory tests that will unequivocally predict protection. The challenge is scheduled to occur approximately 21 days (3 weeks) after the last vaccination visit (Study Day 77) and will be performed in a staggered fashion. The first 56 eligible subjects (28 subjects per study group) will be enrolled and vaccinated (Cohort A). Among the 56 vaccinated individuals a random selection of subjects eligible for challenge will be done according to the local SOP to ensure that a maximum of 46 vaccinated individuals (balanced by group) will progress to the challenge phase. The remaining subjects will not be challenged but will be followed for safety and immunogenicity up to 6 months after the last vaccination.

Unimmunized infectivity control volunteers will also be challenged to verify the adequacy of the challenge. The use of 4 to 6 unimmunized, malaria-naïve controls per challenge day is adequate since the procedure described has generally successfully infected such volunteers [Gordon, 1995]. The challenge of vaccinated subjects from Cohort A will be done at the WRAIR Insectary.

After safety and efficacy assessment for Cohort A, subjects from Cohort B and C (approximately 56 subjects per cohort) will be vaccinated. Of these subjects, a maximum of 46 vaccinated study participants per cohort will progress to the challenge phase. The challenge of Cohorts B and C will be conducted in parallel at WRAIR Insectary and the University of Maryland, CVD, respectively. Malaria-infected mosquitoes for challenge at the University of Maryland will be transported by WRAIR investigators to the insectaries at the University of Maryland for challenge of human subjects.

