**5.4.4.1.3. Cohort A data review by the SMC prior to vaccinations in Cohort B and Cohort C:**

An interim unblinded SMC report including all available safety and reactogenicity data, will be produced by an independent statistician according to an agreed pre-defined Report and Analysis Plan, after the Cohort A has completed the one month post challenge visit. The SMC will review this report prior to authorizing vaccinations to proceed in Cohort B and Cohort C. Vaccination of the next cohort of study participants can be put on hold by the SMC if either of the following sets of holding criteria described below is met:

*Holding rules*

- Solicited local adverse events:
  - More than 25% of Ad35.CS.01 doses are followed by Grade 3 solicited local adverse event beginning within 2 days after Ad35.CS.01 vaccination (day of vaccination and one subsequent day) and persisting at Grade 3 for > 2 consecutive days
  - More than 25% of first doses of RTS,S/AS01B in subjects having received Ad35.CS.01 are followed by Grade 3 solicited local adverse event beginning within 2 days after vaccination (day of vaccination and one subsequent day) and persisting at Grade 3 for > 2 consecutive days
  - More than 25% of second doses of RTS,S/AS01B in subjects having received Ad35.CS.01 are followed by Grade 3 solicited local adverse event beginning within 2 days after vaccination (day of vaccination and one subsequent day) and persisting at Grade 3 for > 2 consecutive days
- Solicited systemic adverse events:
  - More than 25% of Ad35.CS doses are followed by Grade 3 solicited systemic adverse event estimated to be related to vaccination beginning within 2 days

after Ad35.CS.01 vaccination (day of vaccination and one subsequent day) and persisting at Grade 3 for > 2 consecutive days

- More than 25% of first doses of RTS,S/AS01B in subjects having received Ad35.CS.01 are followed by Grade 3 solicited systemic adverse event estimated to be related to vaccination beginning within 2 days after vaccination (day of vaccination and one subsequent day) and persisting at Grade 3 for > 2 consecutive days
- More than 25% of second doses of RTS,S/AS01B in subjects having received Ad35.CS.01 are followed by Grade 3 solicited systemic adverse event estimated to be related to vaccination beginning within 2 days after vaccination (day of vaccination and one subsequent day) and persisting at Grade 3 for > 2 consecutive days

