- Unsolicited adverse events
  - a serious adverse event considered related to vaccination occurs in a study participant from the Ad35.CS.01 – RTS,S/AS01B – RTS,S/AS01B group
  - more than 25% of subjects from the Ad35.CS.01 – RTS,S/AS01B – RTS,S/AS01B group develop any Grade 3 unsolicited adverse event considered related to vaccination and persisting at Grade 3 for > 2 consecutive days.
- Standard neurological evaluation
  - more than 10% of subjects from the Ad35.CS.01 – RTS,S/AS01B – RTS,S/AS01B group develop abnormal neurological symptoms captured by standardized neurological evaluation ([Appendix B](#)).
- Laboratory adverse events
  - more than 25% of subjects from the Ad35.CS.01 – RTS,S/AS01B – RTS,S/AS01B group develop any Grade 3 laboratory adverse event considered related to vaccination.
  - more than 10% of subjects develop hematuria, not taking into account menstruating females if the hematuria coincides with their regular monthly time for their period or urinary tract infection.

If a holding rule has been met, vaccination of subjects in the subsequent cohort will only start if GSK, Crucell, MVI and investigators agree to it, following discussions with the SMC. All IRBs will be notified if a holding rule is activated or released after SMC review.

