### *Individual stopping rules*

In addition to the above stated group holding rules, stopping rules for individual subjects will apply (i.e., indications to withdraw individuals from further vaccinations). These will apply to Cohort A, B and C. The PI will have the responsibility to withdraw from further vaccination individual study participants who present at least one of the following stopping rules for individual subjects:

- Local reactions: upon investigator discretion.

- Systemic solicited adverse events:
  - the subject develops a Grade 3 systemic solicited adverse event beginning within 2 days after vaccination (day of vaccination and one subsequent day) and persisting at Grade 3 for > 2 consecutive days.
- Unsolicited adverse events
  - the subject has any Grade 3 adverse event considered related to vaccination, persisting at Grade 3 for >2 consecutive days.
  - the subject has a serious adverse event considered related to vaccination.
  - the subject has an acute allergic reaction or anaphylactic shock following the administration of vaccine investigational product.
- Laboratory adverse events
  - the subject has any Grade 3 laboratory adverse event considered related to vaccination.
  - the subject, excluding menstruating female, develops hematuria considered related to vaccination.

The PI may, using discretion, ask for the study to be placed on hold and an SMC meeting to be held for any single event or combination of multiple events which, in professional opinion, jeopardize the safety of the subjects or the reliability of the data.

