**Amendment 1**

vA volunteer who develops malaria and has 3 consecutive (separated by greater than 12 hours) negative smears following initial treatment may be excused from the remaining hotel/inpatient facility visits and the late post-challenge clinic visits at Study Day **97, 99, 101 and 103** (20, 22, 24 **and 26 days** post-challenge).

w An interim analysis for futility will be performed on safety and efficacy data collected up to 28 days post-challenge (Study Day 105) for the first 46 subjects vaccinated and challenged (Cohort A). A primary analysis will be performed on all efficacy, immunogenicity and safety data collected up to 28 days post-challenge (Study Day 105) on all cohorts.

z ***One repeat blood drawn is allowed, if necessary, at each time point that a blood sample is taken during the study, at investigators discretion.***

● is used to indicate a study procedure that requires documentation in the individual eCRF

○ is used to indicate a study procedure that does not require documentation in the individual eCRF

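### Section 10.7.1 and Table 9 note w tie the Cohort A interim safety data to the 46 challenged subjects, in conflict with Sections 5.4.4.1.3, 5.4.4.2, 10.5.1 and 10.8.4

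*Protocol*

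**What the plan says.** Two places attach safety data to the challenged subjects. Section 10.7.1 describes an interim analysis for futility "performed on safety and efficacy data collected up to 28 days post-challenge (Study Day 105) for 46 subjects from Cohort A", and adds "Refer to Sections 5.4.4.1 and 5.4.4.2 for more details on the futility analysis". Section 5.4.4.1 is the safety review. Note w to Table 9 (Section 5.5) also speaks of safety and efficacy data, "for the first 46 subjects vaccinated and challenged (Cohort A").

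Four places say otherwise:

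- Section 5.4.4.1.3: "An interim unblinded SMC report including all available safety and reactogenicity data, will be produced by an independent statistician". It continues: "The SMC will review this report prior to authorizing vaccinations to proceed in Cohort B and Cohort C". The holding rules follow in the same section.
- Section 5.4.4.2: the futility analysis of the 46 uses efficacy data. Section 10.7.2 adds that this analysis looks only at stopping for futility.
- Section 10.5.1: the Total vaccinated cohort for safety is everyone with at least one documented vaccination.
- Section 10.8.4: safety is analysed on that cohort.

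On who is challenged, Section 5.4.3 says: "Volunteers from both study groups completing their immunization course will be challenged with sporozoite-infected mosquitoes". It sets Cohort A at 56 vaccinated subjects, 28 per group, with at most 46 going on to challenge, balanced by group.

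**The concern.** The protocol names two populations for the safety side of one interim look. That look decides whether Cohorts B and C are vaccinated, which is two thirds of the planned Ad35.CS.01 recipients.

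The two populations are not interchangeable. A subject who meets an individual stopping rule gets no further vaccine, does not complete the course and so is not challenged. Several of those rules describe the same events as the group holding rules. For example, one individual rule is "the subject has a serious adverse event considered related to vaccination", and one group criterion is "a serious adverse event considered related to vaccination occurs in a study participant" from the ARR group. Safety data limited to challenged subjects would therefore be selected partly on not having had the event being counted. The interim safety report is written to a separate pre-defined analysis plan, which is not shown here. An author who starts from Section 10.7.1 could specify the wrong denominator.

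**Working it through.** **1. Cohort sizes.** Section 4.1 gives 168 enrolled (84 per group) and 138 challenged (69 per group), in three roughly equal cohorts.

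- Vaccinated in Cohort A: 168/3 = 56, or 84/3 = 28 per group.
- Challenged in Cohort A: 138/3 = 46, or 69/3 = 23 per group.
- Vaccinated but not challenged: 56 − 46 = 10, or 5 per group.

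These agree with Section 5.4.3.

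**2. Holding criteria set against the individual stopping rules.** Section 5.4.4.1.3 has 3 local + 3 systemic + 2 unsolicited + 1 neurological + 2 laboratory = 11 group criteria. The last column shows what would happen if only challenged subjects were counted.

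| Group criterion | Matching individual rule | Effect on the challenged subset |
|---|---|---|
| Related Grade 3 systemic event after Ad35.CS.01 | Yes, and broader: relatedness is not required | Numerator 0 |
| The same after the first RTS,S/AS01B dose | Yes, and broader | Numerator 0 |
| The same after the second RTS,S/AS01B dose | Course already complete | Not blocked |
| Related SAE | Yes | Loses events after doses 1 and 2 |
| Related Grade 3 unsolicited event | Yes | Loses events after doses 1 and 2 |
| Related Grade 3 laboratory event | Yes | Loses events after doses 1 and 2 |
| Hematuria, related or not | Only if judged related | Loses cases judged related |
| Neurological findings | None | Not blocked |
| Three local criteria | Investigator discretion | Depends on practice |

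So 2 of the 11 cannot fire on the challenged subset, and 4 are weakened (three in full for doses 1 and 2, hematuria in part).

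**3. Example for the first row.** More than 25% of 28 ARR subjects means at least 8, since 7/28 is exactly 25% and 8/28 = 28.6%. If 8 have the event after Ad35.CS.01, the hold is met on all 28. All 8 also meet the individual rule, so at most 28 − 8 = 20 ARR subjects can be challenged, and that set shows 0 of at most 20. A balanced set of 46 would then be out of reach, since it needs 23 per group.

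**4. Chance that this hold fires.** With X ~ Binomial(28, p), the chance on all ARR vaccinees is P(X ≥ 8). On the challenged subset it is 0 at every p. The rates p are assumptions.

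| Assumed rate p | P(X ≥ 8), all 28 |
|---|---|
| 7% | 0.0005 |
| 13% | 0.023 |
| 25% | 0.40 |
| 30% | 0.64 |
| 40% | 0.93 |

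The first two rates are the severe systemic reactions after the first dose in Table 1: 1/15 at 10^10 vp and 2/16 at 10^11 vp, on either side of the 5×10^10 vp given here. They are of any duration, whereas the hold requires a related event that stays at Grade 3 for more than 2 days.

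**The case against.** A reader might infer that several holds in this trial cannot fire. The text does not support that. The holding rules are written in Section 5.4.4.1.3 and applied by the safety committee to a report of all available data. Their denominators are doses, or subjects in the ARR group, and none mentions challenge. Section 10.7.1 describes a futility analysis and defers to the detailed sections. On the ordinary principle that the specific section governs, the holds run on all vaccinated subjects and work. That part of the objection stands.

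A reader might also infer that a related SAE after dose 1 or 2 would go unseen. It would not. The committee receives all SAEs in real time (5.4.4.1.1). It also reviews reactogenicity, laboratory, unsolicited and neurological listings by group after doses 1 and 2 (5.4.4.1.2). Before dose 3 there is a numeric 25% rule for persistent Grade 3 solicited events in ARR subjects, which largely duplicates the systemic hold after the first RTS,S/AS01B dose. The investigator may also ask for a study hold.

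Nor are the 10 unchallenged subjects all withdrawals. They mix random non-selection among eligible subjects, ordinary drop-out and rule-based withdrawal. At the Table 1 rates the Ad35.CS.01 systemic hold would rarely fire even on all 28, so the contrast of 0.93 with 0 depends on an assumed 40% rate.

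One gap remains. Section 5.4.4.1.2 sets no stopping rule between doses 1 and 2. The Cohort A review is therefore the only place with a numeric group rule for solicited events after Ad35.CS.01, and its systemic criterion is one of the two that the 46-subject reading would empty.

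**Conclusion.** The contradiction is in the current text and should be reconciled. Section 10.7.1 and note w attach safety data to the 46, while Sections 5.4.4.1.3, 5.4.4.2, 10.5.1 and 10.8.4 together place safety on all vaccinated subjects and keep the 46 for efficacy futility. It is a conflict of wording with a safety consequence if the wrong passage is followed, not a failure of the holding rules as written.

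If the 46 were used, two of the 11 criteria would be empty and four weakened. This assumes that the individual stopping rules are applied as stated and that no one withdrawn from vaccination is challenged. The probabilities in the working are conditional on assumed event rates and do not predict what this trial would show.

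**What to change.** In Section 10.7.1 and Table 9 note w, limit the 46 challenged subjects, worded as at most 46, to the efficacy futility estimate of Section 5.4.4.2. Add that the Cohort A interim safety and reactogenicity tabulations, and the holding-rule denominators, cover every Cohort A subject with at least one documented dose (about 28 per group), as Section 5.4.4.1.3 implies. Check that the analysis plan for the safety committee's report uses the same population.

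The cost is about one sentence in each place. The data are already collected, because unchallenged subjects stay in safety follow-up. No threshold, stopping rule or other clinical rule changes.

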#### **10.7.2. Statistical considerations for interim analyses**

An interim analysis for futility is planned on 46 subjects from cohort A. Analysis will be performed by a statistician external to the GSK-MVI-Crucell clinical teams and summary results will be communicated without unblinding individual trial subjects. In the event the trial is stopped for futility, the databases will be cleaned and locked and a clinical study report will be written. In the event the trial continues no clinical study report will be generated. However, in any case the database and analyses will be appropriately stored. As this analysis only looks at stopping for futility, no corrections of the overall alpha level are required.

#### **10.8. Statistical methods**

Analyses will be performed by cohort (A, B, C) and pooled across cohort where applicable and will be further specified in the statistical analysis plan.

##### **10.8.1. Analysis of demographics/baseline characteristics**

- Demographic characteristics (age in years, gender and geographic ancestry) of each study cohort will be tabulated per group.
- The distribution of subjects enrolled among the study centers will be tabulated.

##### **10.8.2. Analysis of efficacy**

Efficacy will be assessed on the ATP cohort for efficacy by comparison of malaria incidence and time to onset of parasitemia after sporozoite challenge. Vaccine efficacy is defined as  $100 \times (1 - \text{Relative Risk})$ . Fisher's Exact test will be used for the comparison of malaria incidence between the two vaccinated groups. Kaplan-Meier analysis will be performed on time to onset of parasitemia, with testing between the two treatment groups using the log-rank statistic. Relative risk of infection and 95% confidence intervals (95% CI) will be calculated. All statistical tests will be two-tailed at 5% significance level.

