### **1.2.2. Rationale for the study design**

This study is designed to evaluate safety, reactogenicity, immunogenicity and efficacy of Crucell's candidate replication deficient adenovirus type 35 circumsporozoite malaria vaccine (Ad35.CS.01) administered intramuscularly followed one month later by two doses of GSK Biological's malaria candidate vaccine RTS,S/AS01B administered intramuscularly at one month intervals, compared to three doses of RTS,S/AS01B administered intramuscularly at one month intervals in healthy malaria-naïve volunteers aged 18 to 50 years. The sporozoite challenge model, in the RTS,S/AS candidate vaccine development program, has demonstrated a high relevance in its ability to predict efficacy under conditions of natural exposure in malaria-endemic countries. Approximately 168 participants will be enrolled in the study. Three cohorts of approximately equal size will be enrolled, vaccinated then challenged separately. This design takes into account logistical restrictions on the size of human challenge procedures and allows for a futility analysis to be conducted after the results of the malaria challenge in the first cohort. The proposed study design is such that the sample size will provide 80% power to demonstrate a 50% increase in efficacy of an immunization regimen including an initial dose of Ad35.CS.01 over efficacy of a regimen based on RTS,S/AS01B alone, assuming 50% vaccine efficacy of the RTS,S/AS01B group over challenge infectivity controls.

The study design is similar to that of other past studies successfully conducted. Healthy adults will be enrolled and followed up in closely controlled conditions by investigators

experienced in *P. falciparum* challenge studies. Immunological investigations are planned with the intent to characterize qualitatively and quantitatively the immune response induced by the immunization regimen and assess the presence of a correlation of specific effector immune function(s) with protection against malaria infection in the sporozoite challenge model. Protection will be evaluated by the proportion of immunized participants who remain free of *P. falciparum* infection following sporozoite challenge and by a delay in the pre-patent period leading to infection.

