#### **5.2.2.2. Treatment allocation to the subject**

The treatment allocation at the investigator site will be performed using an online central randomization system (SBIR). The treatment numbers will be allocated by kit. The randomization algorithm will use a minimisation procedure accounting for center.

When SBIR is not available, please refer to the SBIR user guide or the SPM for specific instructions.

After having checked the eligibility of the subject and obtaining the ICF, the site staff in charge of the vaccination will access SBIR. Upon providing the subject identification number, the randomization system will use the minimisation algorithm to determine the

treatment number to be used for the subject. Each treatment number must be recorded in the eCRF on the Vaccine Administration screen.

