### 10.4. Estimated sample size

For the final analysis, the target enrollment for this study will be 168 volunteers to ensure 69 subjects per study groups will undergo sporozoite challenge, given an approximate 20% estimated drop-out rate, based on past experience.

For the primary endpoint, the study will have 82% power to demonstrate an increase of 50% efficacy (2-sided Fisher exact test,  $\alpha=5\%$ ) of the ARR group over the RRR group, assuming a 50% attack rate in the RRR group. The increase in VE of the ARR group over the RRR alone group is defined as  $100 \times (1 - \text{AR}_{\text{Ad35.CS}} / \text{AR}_{\text{RTS,S}})$  where AR is the attack rate in the 2 groups.

The trial will have 80% power (2-sided Fisher exact test,  $\alpha=5\%$ ) to detect the following fold increase in AE rates of the ARR group over the RRR group (right column), depending on the rate of AEs in the RRR group (left column) (see [Table 30](#)).

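### Stratifying the primary Fisher test and the log-rank test by cohort would be a free improvement; the planned tests are valid and the stated 82% power is correct

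*Protocol*

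**What the plan says.** The analysis text fixes the tests. Section 10.8.2 states that Fisher's "Exact test will be used for the comparison of malaria incidence between the two vaccinated groups", adds a Kaplan-Meier analysis with a log-rank test, and closes with "All statistical tests will be two-tailed at 5% significance level". No cohort or center term appears in either test.

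The power statement in section 10.4 uses the same pooled test: "the study will have 82% power to demonstrate an increase of 50% efficacy (2-sided Fisher exact test", with alpha 5%, "assuming a 50% attack rate in the RRR group", on an enrolment meant "to ensure 69 subjects per study groups will undergo sporozoite challenge".

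The design is grouped. Section 5.2.2.2: "The randomization algorithm will use a minimisation procedure accounting for center". Section 1.2.2: "Three cohorts of approximately equal size will be enrolled, vaccinated then challenged separately". Section 3 caps each cohort at 46 challenged vaccinees, balanced by group, so 23 per group. Section 5.4.3 places the challenges of Cohorts A and B at WRAIR and that of Cohort C at the University of Maryland.

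Section 10.8 adds: "Analyses will be performed by cohort (A, B, C) and pooled across cohort where applicable", with further detail left to the statistical analysis plan.

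**The concern.** The design balances the groups within center and, at challenge, within cohort, but the two named tests ignore both. When arms are balanced within strata and the strata have different event rates, a pooled test overstates the variance of the treatment difference and becomes conservative. What is at stake is some power that the same 138 challenged subjects could deliver at no extra cost.

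The protocol makes different attack rates plausible without giving any figure. Cohort A is challenged and reviewed before B and C are vaccinated. Each challenge day has its own infectivity controls. Mosquitoes are transported for Cohort C (section 5.4.3). Smear samples are handled differently at the two centers (section 5.6.4.3).

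**Working it through.** **Inputs.** From section 10.4: 69 challenged per group, attack rate 0.50 in RRR, 50% efficacy (relative risk 0.5, so 0.25 in ARR), two-sided Fisher test at 5%. From section 3: three cohorts with 23 per group each. Assumed, because the protocol gives no figure: RRR rates by cohort of 50/50/50, 40/50/60, 30/50/70 and 20/50/80%.

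**Step 1, the plan's own figure.** Power = Σ over x, y of Bin(x; 69, 0.50) · Bin(y; 69, 0.25) · 1[Fisher p ≤ 0.05] = 82.3%, against 82% stated. It reproduces. The exact size of this test at a common rate of 0.5 is 3.3%.

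**Step 2, why pooling is conservative under spread.** With 23 per group in each cohort, the CMH test uses E = m/2 and V = 23·23·m(46 − m)/(46²·45) = m(46 − m)/180 per cohort, where m is the number of infections in that cohort. Its numerator, ARR infections minus expected, is the same as in the pooled test; only the variance differs. At 30/50/70% under the null, the pooled variance uses 0.5 × 0.5 = 0.25, while the within-cohort average is (0.21 + 0.25 + 0.21)/3 = 0.223. The ratio is 0.893, with square root 0.945, so an unstratified Pearson test has an effective critical value of 1.96/0.945 = 2.07 and a size of about 3.8%. Simulation gives 3.8%. Fisher's discreteness takes it lower still.

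**Step 3, simulated size** (40,000 trials per scenario):

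| Rates, both groups | Pooled Fisher | Pooled Pearson | Exact stratified | CMH, uncorrected |
|---|---|---|---|---|
| 50/50/50 | 3.3% | 5.0% | 3.3% | 5.0% |
| 30/50/70 | 2.4% | 3.8% | 3.3% | 4.9% |
| 20/50/80 | 1.4% | 2.4% | 3.2% | 4.9% |

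**Step 4, simulated power at relative risk 0.5 in every cohort:**

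| RRR rates | Pooled Fisher | Pooled Pearson | Exact stratified | CMH, uncorrected |
|---|---|---|---|---|
| 50/50/50 | 82.5% | 86.5% | 82.7% | 86.4% |
| 40/50/60 | 82.6% | 86.5% | 83.4% | 87.0% |
| 30/50/70 | 83.2% | 87.2% | 85.5% | 89.2% |
| 20/50/80 | 84.4% | 88.5% | 88.8% | 91.9% |

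The simulation standard error of one entry is about √(0.83 × 0.17/40,000) = 0.2 points. Differences below are taken before rounding.

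**Step 5, separating the two sources of gain.**
- Stratification alone (exact stratified minus Fisher): 0.1, 0.7, 2.3 and 4.4 points.
- Fisher to uncorrected CMH: 3.9, 4.4, 6.0 and 7.5 points. Of this, moving from Fisher to the unstratified Pearson test already gives 3.9, 3.9, 4.0 and 4.0. That part has nothing to do with cohorts.
- With a continuity correction, CMH gives 82.3, 82.9, 85.3 and 88.5%, close to the exact stratified test. The larger gain therefore depends on leaving the correction out.

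**Step 6, variations.** Stratifying on the two centers only gains 0.1 points with equal rates and 2.0 with RRR rates of 40% and 70%. If a constant odds ratio of 1/3 is assumed instead of a constant relative risk, stratification alone gains 1.1, 4.1 and 10.7 points at ±10, ±20 and ±30. Section 10.8.2 defines efficacy through the relative risk, so the constant relative risk is the closer reading.

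**Step 7, the estimate.** The Mantel-Haenszel relative risk is Σ(aᵢ·23/46)/Σ(cᵢ·23/46) = Σaᵢ/Σcᵢ, where aᵢ and cᵢ are the ARR and RRR infections in cohort i. With equal arms in each cohort it is identical to the crude relative risk.

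**The case against.** A reader might infer that pooling costs the trial 4 to 6 points of power. The documents do not support that. At the protocol's own single 50% attack rate, a like-for-like comparison shows about 0.1 points; the jump to 86% is the price of an exact test, and an unstratified Pearson test recovers it equally. Strict error control is a defensible choice.

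A reader might also infer that the type I error or the stated power is wrong. Neither is: pooling makes the test more conservative, not less, and in the scenarios with relative risk 0.5 the planned test holds 82% or more. Nor is the pooled relative risk distorted when arms are balanced within cohort. It could move slightly only if exclusions from the according-to-protocol cohort unbalance them.

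It is tempting to add that each cohort has its own mosquito batch. The protocol does not say so. Cohorts B and C are challenged in parallel with mosquitoes reared at one place, the exposure is standardised to five infected mosquitoes with a minimum gland score, and slides follow one validated procedure. Differences between cohorts are plausible but unquantified.

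Finally, section 10.8 leaves detail to the statistical analysis plan, which was not available here. That sentence covers by-cohort and pooled presentation. It adds no stratum to the tests that section 10.8.2 names, so the suggestion still belongs in that section. The other objections stand and limit the point to efficiency.

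**Conclusion.** A free improvement, not an error. The planned test is valid and its 82% power is correct. With relative risk 0.5, naming cohort as a stratum gains about 0.1 points if cohorts have equal attack rates, 0.7 at ±10 percentage points and 2.3 at ±20. It lost nothing material in any scenario tried. The conservatism it removes is the fall in the Fisher test's size from about 3.3% to 2.4% at 30/50/70%. An uncorrected CMH test gains about 4 to 6 points over the same range, but about 4 of these come from replacing an exact test with an asymptotic one. The size of the benefit rests on an assumed spread and on 23 per group per cohort. No power was calculated for a stratified log-rank test.

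**What to change.** In section 10.8.2, name cohort (A, B, C) as the stratification factor for the primary test and for the log-rank test. Cohort also separates the two centers at challenge. Choose either the exact stratified test or CMH for the primary comparison, and if CMH, state whether a continuity correction applies. Keep the pooled Fisher test as a sensitivity analysis.

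In section 10.4, align the test named in the power statement. Under equal rates the figure stays at about 82 to 83% for the exact stratified test and becomes about 86% for uncorrected CMH.

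The cost is a short edit to two sections and a restated power line, made before any unblinding. No extra subjects or data are needed.
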